### Inclusion and exclusion criteria

Inclusion and exclusion criteria are summarized in Table 1.

**Table 1 Tab1:** *Project ENHANCE* Inclusion and Exclusion Criteria

Inclusion criteria: *all criteria must be met*	Exclusion criteria: *excluded if one or more of these criteria are met*
1) Are hospitalized at YNHH on a general medical ward	1) Been engaged in formal AUD treatment in the past 30 days (i.e., excluding mutual help groups, such as Alcoholics Anonymous)
2) Have an AUDIT-C score ≥ 7	2) Meet DSM-5 criteria for untreated moderate to severe opioid use disorder
3) Meet Diagnostic and Statistical Manual (DSM-5) criteria for a moderate to severe AUD (regardless of primary reason for hospitalization) consistent with clinical guidelines for MAUD initiation	
4)≥ 1 heavy drinking day in the 30 days prior to hospitalization	3) Self-reported or have urine testing confirming pregnancy, nursing, or trying to conceive
5) Are ≥ 18 years old	4) A life-threatening or unstable medical, surgical, or psychiatric condition that prohibits study participation
6) Willing to consider MAUD	5) Inability to provide ≥ 1 form of contact information
7) Are willing and able to be contacted for follow-up	6) Anticipate being unable to return for follow-up assessments for any reason, such as travel, planned procedure
	7) Inability to understand English or Spanish
	8) Currently in jail, prison or other overnight facility as required by court of law and/or is considered a prisoner under local law or is under current terms of civil commitment or guardianship

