**Alcohol-related measures**				
Alcohol use history (lifetime, past 30 days)	Description, moderator	X		
AUDIT-C [43]	Description, moderator	X		
Alcohol symptom checklist [46]	Description, moderator	X		X
Alcohol timeline followback [109]	Secondary outcome	X	X	X
Formal alcohol treatment [110] and MAUD adherence [55]	Primary outcome	X	X^b^	X^b^
Phosphatidylethanol (PEth) [111]	Secondary outcome	X	X	X
Perspectives on treatment for alcohol use disorder [112, 113]	Description, moderator	X		
Alcohol readiness ruler	Description, moderator	X^a^	X^b^	X^b^
Alcohol abstinence self-efficacy scale [114]	Mediator	X^a^	X^a^	X^a^
Short Inventory of problems-revised [115]	Secondary outcome	X^a^		X^a^

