#### Statistical analyses

##### Primary and secondary outcomes

The primary objective of this analysis will be to determine if the proportion of participants with formal AUD treatment engagement (yes/no) at 34 days post-discharge differs among those randomized to BNI alone, BNI + MAUD, and BNI + MAUD + CBT4CBT in this diverse sample. The primary outcome (1a) of AUD treatment engagement is binary and we will use logistic regression with two planned contrasts to evaluate statistical significance of the differences in proportion of formal AUD treatment engagement (as verified through electronic medical record and/or contact with treatment facility). This statistical model will also be used to assess efficacy of study interventions on AUD treatment engagement at 90-days following randomization (1a). Secondary outcomes (1b) will include change in the self-reported percentage of heavy drinking days (PHDD) by month from the 30-day period prior to hospitalization (baseline) to the 34- and 90-day post-discharge timepoint, which will be evaluated with random effects regression statistical models. These models have several advantages in follow-up data from clinical trials of individuals who use substances, as they are less vulnerable than traditional MANOVA approaches to missing data [85, 86]. An additional secondary outcome will include change in biomarker PEth, which as a continuous outcome will be evaluated with a similar statistical approach. Given limited data on factors impacting PEth levels among hospitalized patients [87] and building from our own experiences [88], we will also evaluate the correlation between baseline self-reported alcohol use (in the 30-day period prior to hospitalization) and PEth levels (e.g., liver disease, hemoglobin [38]), factors associated with PEth levels adjusting for baseline self-reported alcohol use, and factors impacting change in PEth from baseline to follow-up. Exploratory outcomes of healthcare utilization, including rates and costs of emergency department visits and hospital readmissions during the 34- and 90-day post-discharge period will be evaluated with mixed model ANOVAs. Analysis of treatment effects on primary, secondary, and exploratory outcomes will include the following contrasts: *H1:* BNI + MAUD > BNI; BNI + MAUD + CBT4CBT > BNI + MAUD or BNI.

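### The heavy-drinking-day and PEth outcomes are defined as change with no baseline term stated for the arm comparison; read as written, this has change-score precision, and adjusting for baseline is a free improvement

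*Protocol article*

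**What the plan says.** Under Statistical analyses, Primary and secondary outcomes, the protocol article lists "change in the self-reported percentage of heavy drinking days" from the 30 days before hospitalization to the 34- and 90-day timepoints, "which will be evaluated with random effects regression statistical models". The biomarker follows the same route: "change in biomarker PEth, which as a continuous outcome will be evaluated with a similar statistical approach". The Exploratory outcomes section reuses random effects regression for change in alcohol use within and across racial and ethnic groups.

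Baseline adjustment is mentioned once in the outcome analyses, and for a different purpose: the study of "factors associated with PEth levels adjusting for baseline self-reported alcohol use". For the arm comparison, the article does not say whether baseline is a covariate, a repeated response or a subtracted quantity. Nor does it say whether baseline means are held equal across arms.

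Table 2 schedules both timeline followback and PEth at baseline, day 34 and day 90.

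**The concern.** Randomised arms share the same expected baseline, so the baseline value can be used purely to reduce noise. Subtracting it in full uses it with a fixed coefficient of one. Adjusting for it lets the data set the coefficient.

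A low correlation between baseline and follow-up is plausible here. Entry requires an AUDIT-C score of at least 7 and at least one "heavy drinking day in the 30 days prior to hospitalization", and follow-up comes after an acute admission with treatment referral in every arm. A low correlation is where full subtraction costs most.

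At stake is the precision of the two main secondary alcohol-use outcomes, and of the same outcomes within smaller racial and ethnic groups. A chance baseline difference between arms also passes into a change-score contrast. The urn described under Recruitment and randomization balances AUD severity, but not PHDD or PEth themselves.

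**Working it through.** **Inputs from the article.** 150 per arm, 20% loss of data, hence 150 × 0.8 = 120 per arm; alpha 0.025 per contrast (Justification of sample size). That section sizes only the binary primary outcome, so there is no stated figure for PHDD or PEth to reproduce.

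**Assumed inputs.** Correlation rho between baseline and follow-up, from 0.2 to 0.7; ratio k of baseline to follow-up variance; and, for the power illustration only, a 0.35 SD difference and two-sided testing. None of these is in the documents.

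**Step 1: variance of the arm contrast, relative to analysing follow-up alone (= 1).**
- Change score: 1 + k − 2·rho·√k, which is 2(1 − rho) when k = 1.
- Baseline-adjusted: 1 − rho², whatever k is.

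**Step 2: equal variances (k = 1).** The ratio is 2(1 − rho)/(1 − rho²) = 2/(1 + rho).

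| rho | Change | Adjusted | Sample ratio |
|---|---|---|---|
| 0.2 | 1.60 | 0.96 | 1.67 |
| 0.3 | 1.40 | 0.91 | 1.54 |
| 0.5 | 1.00 | 0.75 | 1.33 |
| 0.7 | 0.60 | 0.51 | 1.18 |

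**Step 3: baseline variance half the follow-up variance (k = 0.5).** The change-score variance is 1.5 − 1.414·rho.

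| rho | Change | Adjusted | Excess sample |
|---|---|---|---|
| 0.2 | 1.217 | 0.96 | 27% |
| 0.3 | 1.076 | 0.91 | 18% |
| 0.5 | 0.793 | 0.75 | 6% |
| 0.7 | 0.510 | 0.51 | 0% |

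With k = 2 the loss grows: at rho = 0.3 the change-score variance is 2.151, and 2.151/0.91 = 2.36.

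**Step 4: when subtraction is worse than ignoring baseline.** This needs 1 + k − 2·rho·√k > 1, that is rho < √k/2 = SD_baseline/(2·SD_follow-up). The threshold is 0.35 at k = 0.5, 0.50 at k = 1 and 0.71 at k = 2.

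**Step 5: does the longitudinal model avoid the loss?** A generalised least squares calculation with three time points, complete data, equal variances and a common correlation gives two answers:
- Free baseline means by arm: 1.40 at rho = 0.3 and 1.00 at rho = 0.5, exactly the change-score values.
- Common baseline mean: 0.91 and 0.75, exactly the adjusted values.

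Both models are random effects regression, so the name of the method does not settle the matter.

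**Step 6: illustrative power.** Power = Φ(0.35/√(2v/120) − 2.241), with k = 1 and v from Step 2.

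| rho | Change | Follow-up only | Adjusted |
|---|---|---|---|
| 0.3 | 52% | 68% | 73% |
| 0.5 | 68% | 68% | 81% |
| 0.7 | 90% | 68% | 94% |

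**Step 7: chance imbalance.** If the arms differ by D at baseline, the expected follow-up difference is the treatment effect plus rho·D (k = 1). After subtraction the error is (rho − 1)·D: 70% of the imbalance with reversed sign at rho = 0.3, and 30% at rho = 0.7. Over repeated randomisation D averages zero, so this is not a systematic bias.

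**The case against.** The strongest reply is that the article never says baseline is left out. A change outcome regressed on arm with baseline as a covariate gives the same treatment estimate as modelling the follow-up value with that covariate, and a random effects model with a common baseline mean recovers full precision. Either would fit the published wording, and a condensed article commonly leaves covariates and parameterisation to the full protocol or analysis plan. This stands as far as it goes: a reader might infer that the plan has decided to test change without conditioning on baseline, and the text does not support that. The loss attaches to the most direct reading of the wording, not to a declared choice.

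The objection to the magnitude also stands. Equal variances are an assumption, and selecting recent heavy drinkers could shrink the baseline variance, which reduces the loss (Step 3). The criterion of one heavy drinking day in 30 is, however, a weak restriction on PHDD. The documents support neither direction, and the 0.35 SD effect is only illustrative.

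Two further inferences are tempting and unsupported. One is that subtraction here does worse than ignoring baseline; that needs rho below a threshold that depends on two unreported SDs. The other is that the treatment effect is biased; under randomisation the change-score contrast is unbiased on average, and balancing AUD severity may further limit imbalance in drinking.

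The reply does not remove the point. The article does fix change as the outcome and mentions baseline adjustment only for correlates of PEth level. The alternative is no less precise in large samples at any rho or k, so recommending it does not depend on guessing either.

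**Conclusion.** The point holds as a matter of precision on secondary outcomes. Read as written, the PHDD and PEth contrasts have change-score precision. Under equal variances that costs 18% to 67% more participants over rho = 0.7 to 0.2; with half the baseline variance it costs about 0% to 27%. These figures rest on assumed correlations and variance ratios and on complete data. The primary outcome, its sample size and the validity of the randomised comparison are untouched. The change is worth making as a free improvement; it does not correct an error that invalidates the analysis.

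**What to change.** State in the analysis text that the day-34 and day-90 values of PHDD and PEth are the outcomes of the random effects model, with the baseline value of the same measure as a covariate. Equivalently, keep baseline in the response vector and constrain the arm means to be equal at baseline. Take the planned arm contrasts at each time point from that model, and use the same form in the exploratory subgroup analyses. Change from baseline can still be reported descriptively.

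The cost is analysis wording only: no extra participants, visits or assays, because both baseline measures are already on the Table 2 schedule. If the full analysis plan already specifies one of these forms, nothing needs to change beyond saying so.

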## Methods

### Overall design

Funded by the National Institute on Alcohol Abuse and Alcoholism, *Project ENHANCE* is a three-arm randomized clinical trial that aims to enroll a diverse sample of individuals with untreated AUD (n = 450) during their acute medical hospitalization at a large urban hospital in the US northeast. We will compare the effectiveness of three treatment engagement strategies on the primary outcome of AUD treatment engagement at the 34th day post-hospital discharge (Aim 1, Fig. 2): (1) Brief Negotiation Interview (with referral and telephone booster) alone (BNI), (2) BNI plus facilitated initiation of MAUD (BNI + MAUD), or (3) BNI + MAUD + initiation of computer-based training for cognitive behavioral therapy (CBT4CBT, BNI + MAUD + CBT4CBT). Secondary outcomes include AUD treatment engagement on the 90th day post-hospital discharge and changes in self-reported alcohol use (percentage of heavy drinking days by Timeline Followback) and the alcohol biomarker, phosphatidylethanol (PEth). Exploratory outcomes based on self-report and the electronic medical record include health care utilization, such as emergency department visits and hospital readmission. We will additionally explore whether the effectiveness of the interventions on AUD treatment engagement and alcohol use outcomes differ across and within racialized and ethnic groups based on SDOH (Aim 2). In parallel and consistent with a hybrid type 1 effectiveness-implementation approach [20], we will conduct an implementation-focused process evaluation [21] that includes costs, cost-effectiveness, and cost–benefit analyses comparing the three intervention combinations (Aim 3).

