
### Study aims and hypotheses

Among 450 hospitalized individuals with untreated moderate to severe AUD (by Diagnostic and Statistical Manual-5 [DSM-5] criteria), our aims are to evaluate the effectiveness of hospital-initiated BNI vs. BNI + MAUD vs. BNI + MAUD + CBT4CBT on AUD treatment engagement at 34 days (primary outcome) and 90 days post-discharge; changes in alcohol use by self-report and biomarker over the 90 day period; and (exploratory) health care utilization, including Emergency Department visits and hospital readmission (Aim 1). We hypothesize that BNI + MAUD + CBT4CBT will be more effective than BNI + MAUD, which will be more effective than BNI alone as evidenced by higher rates of AUD treatment engagement, and reductions in alcohol use and urgent and emergency healthcare utilization post-discharge.

We will explore whether the effectiveness of the interventions on AUD treatment engagement and alcohol use outcomes differs across and within racial and ethnic groups and by SDOH indicators that reflect sequalae of structural racism (Aim 2). We hypothesize that there will be no difference in treatment effectiveness by race or ethnicity after adjustment of confounders but there will be differences based on SDOH.

Consistent with our prior experiences [40], we will additionally conduct an implementation-focused process evaluation [21], involving process measures, a clinician and staff survey, in addition to obtaining measures of the amounts and unit costs of resources used to implement each intervention to patients as well as health care staff. Analyses of cost, cost effectiveness, possible cost-savings benefits from reduced use of health care following the intervention, and cost–benefit for each intervention will compare individual-level provider and patient costs, indices of cost-effectiveness, and indices of cost–benefit for the three intervention combinations, as well as intervention-level indices of incremental cost-effectiveness ratios (ICERs) [41, 42] (Aim 3).

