**Implementation-related measures**				
Cost-related data	Cost effectiveness	X	X	X
Participant satisfaction	Evaluation		X^a^	X^a,c^

^a^Indicates participant self-administered via survey

^b^Verified with objective measures at follow-up for outcome ascertainment [55, 131]

^c^Completed at 90 day assessment only if not completed at 34 day assessment

A secondary outcome of AUD treatment engagement is potential change in use and cost of health services from before the index hospitalization to a comparable period following hospital discharge. Reduction in health service use and costs would be a cost-savings outcome (i.e., benefit of the intervention) [58]. Even if these health service use and cost savings do not completely compensate for intervention costs, they could at least reduce net intervention cost. Emergency department, outpatient, and inpatient visits as well as medication before and after hospitalization will be extracted from the electronic health record for the 12 months before and following hospitalization. Intervention costs themselves will be assessed by multiplying provider and patient time spent for each patient in each intervention condition by provider and patient self-reported wage rates including employment perquisites, plus any materials, medication, and other resources used in interventions. These costs, and costs of computers and software used in CBT4CBT conditions will be assessed using methods developed in previous research published by several of the current authors [58].

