### Statistical considerations

#### Justification of sample size

Power for the three-arm trial was estimated based on an alpha of 0.025, which is a Bonferroni correction for multiple comparisons, given three treatment conditions with two planned contrasts. We assumed a 40% base rate in engagement in AUD treatment at 34-days post-discharge (primary outcome) following BNI based on our YAMCS post-discharge data and published reports from other hospital-based addiction medicine consult services [13]. A sample size of 450 (150 per condition) will provide adequate power (> 80%) to detect a 15% increase in engagement from the comparator treatment (BNI + MAUD or BNI + MAUD + CBT4CBT) at 34-days, consistent with a small to medium effect (delta = 0.34). With a sample size of 360 participants (120 per condition), we would have > 80% power to detect a 20% increase in engagement, consistent with a medium effect (delta = 0.46). Thus, with a randomized sample of 450, we will have adequate power to detect a medium effect on AUD treatment engagement, assuming a 20% loss of data at follow-up. This is based on experiences with similar populations at YNHH [65], as well as those in our prior outpatient treatment studies [34, 74, 76].

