Intervention-level cost per engaged patient will be calculated, along with increments in this cost as successive interventions are added. We will conduct analyses to determine the type, amount, and monetary values (i.e., costs) of the major resources used to implement each intervention for each patient, including time of professionals and patients, medication, and other intervention materials and resources. Combining cost with effectiveness data for individual patients will make possible descriptive scattergrams and group-level graphs of effectiveness = *f* [costs] and benefits = *f*[costs] as well as statistical analyses comparing effectiveness/cost ratios (e.g., change in PHDD per $100 of resources consumed by intervention) and other indices of relationships between costs and effectiveness for patients in each intervention condition. Average and median effectiveness/cost will be compared statistically for each condition with individual-level effectiveness and costs [58]. Cost per effectively treated patient also will be calculated at the group level, defining effective treatment according to quantitative definitions of clinically meaningful change in alcohol use. Similar analyses will examine graphically and statistically cost–benefit relationships as expressed by individual-level net benefit (i.e., reduction following intervention in costs of ED and readmission minus costs of intervention) [58]. Further, building on a mixed-methods evaluation that informed the study protocol [44], we will conduct a survey of hospital-based clinicians and staff upon conclusion of the clinical trial regarding their perspectives on the alcohol treatment interventions and necessary supports to sustain delivery of these interventions outside of the research infrastructure. We will also capture factors that may contribute to inequitable care among historically minoritized racial and ethnic groups.

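### As described, the exploratory ED-visit and readmission models compare post-discharge values only; adding the prior-12-month value, already being extracted, as a covariate would gain precision at almost no cost

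*Protocol article*

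**What the plan says.** In the Protocol article, the statistical section on primary and secondary outcomes states that "rates and costs of emergency department visits and hospital readmissions during the 34- and 90-day post-discharge period will be evaluated with mixed model ANOVAs". It applies the between-arm comparisons to these outcomes as well: "Analysis of treatment effects on primary, secondary, and exploratory outcomes will include the following contrasts". The same paragraph brings in baseline values for other outcomes. Heavy drinking days are analysed as change from the 30 days before hospitalization, and PEth is analysed as change. For utilization it names none.

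The overall design section sets the status and source of the outcome: "Exploratory outcomes based on self-report and the electronic medical record include health care utilization, such as emergency department visits and hospital readmission". The aims section hypothesizes that the more intensive arms will show "higher rates of AUD treatment engagement, and reductions in alcohol use and urgent and emergency healthcare utilization post-discharge".

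The data collection section (text after Table 2) says that ED, outpatient and inpatient visits and medication "will be extracted from the electronic health record for the 12 months before and following hospitalization". Its stated purpose is "potential change in use and cost of health services from before the index hospitalization to a comparable period following hospital discharge". The process evaluation section uses the same history for individual net benefit, defined as "reduction following intervention in costs of ED and readmission minus costs of intervention".

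**The concern.** How often a patient used the ED or was admitted in the past year is the natural baseline value for how often that patient will do so after discharge. If it is left out of the model, stable differences between patients go into the error term. Prior use is not one of the urn randomization factors (race and ethnicity, sex, Spanish language preference, AUD severity), so the design does not balance it either.

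The trial states a directional hypothesis about urgent and emergency use, but the sample size was set for treatment engagement only. Precision on utilization is therefore whatever 150 per arm happens to give, over short windows and for outcomes that are usually skewed by a few frequent users. A pre-randomization covariate that is already being collected would sharpen these contrasts.

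**Working it through.** **No figure to reproduce.** The documents give no event rate, SD, correlation or power for utilization. Everything below on r is an assumption shown over a range.

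**Inputs from the documents.** 450 participants, 150 per arm; 120 per arm after the assumed 20% loss; alpha 0.025 per contrast. That alpha comes from the sample size section ("Power for the three-arm trial was estimated based on an alpha of 0.025, which is a Bonferroni correction for multiple comparisons"), which concerns the primary outcome. I borrow it for illustration and take it as two-sided, since the section does not say.

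**Step 1: effect of adjustment.** Let r be the correlation between the prior-12-month value and the post-discharge value. Adjustment multiplies the variance of an arm contrast by 1 − r². Then:

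- Minimum detectable difference (MDD) at 80% power, in SD units = (2.241 + 0.842) × √(2/n) × √(1 − r²). With n = 150 and r = 0 this is 3.083 × 0.1155 = 0.356.
- Power for a contrast that has 80% unadjusted = Φ(3.083/√(1 − r²) − 2.241). At r = 0.5 this is Φ(3.560 − 2.241) = Φ(1.319) = 0.906.

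| r (assumed) | Variance factor | MDD, 150 per arm | MDD, 120 per arm | Power |
|---|---|---|---|---|
| 0 | 1.00 | 0.356 | 0.398 | 80% |
| 0.2 | 0.96 | 0.349 | 0.390 | 82% |
| 0.3 | 0.91 | 0.340 | 0.380 | 84% |
| 0.4 | 0.84 | 0.326 | 0.365 | 87% |
| 0.5 | 0.75 | 0.308 | 0.345 | 91% |
| 0.6 | 0.64 | 0.285 | 0.318 | 95% |

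**Step 2: what r might be.** Assume each patient has a stable visit rate drawn from a gamma distribution with shape k, and Poisson counts. With prior mean m₁ and post-discharge mean m₂ = m₁ × days/365,

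r = (m₁m₂/k) / √[(m₁ + m₁²/k)(m₂ + m₂²/k)].

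Worked case: 2 visits a year, k = 1, 90 days. Then m₂ = 0.493 and r = 0.986/√(6 × 0.736) = 0.47, a variance cut of 22%. Over assumed rates of 1 to 4 visits a year and k from 0.5 to 2:

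- 34 days: r from 0.12 to 0.62, variance cut 1.5% to 38%.
- 90 days: r from 0.19 to 0.77, variance cut 3.7% to 59%.

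These figures assume fully stable patient rates. If only 60% of patients keep their rate, r shrinks by that factor. At 2 visits a year, k = 0.5 and 34 days, it falls from 0.47 to 0.6 × 0.47 = 0.28, and the power gain from an 80% start falls from about 9 points to about 3. The model covers counts; r for costs is equally unknown.

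**Step 3: simulation check.** 4,000 null trials, 120 per arm, 2 visits a year, k = 1, 90 days. The SE of the arm difference was 0.107 unadjusted and 0.095 adjusted, a variance ratio of 0.80. Both estimates centred on zero.

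**Step 4: does the planned change analysis do the same job?** For periods of equal length and equal variance, a change score has variance factor 2(1 − r), with r now the equal-period correlation: 1.6 at r = 0.2 and 1.0 at r = 0.5. Below 0.5 it is less precise than ignoring the baseline. In the worked case the 90-day to 90-day correlation is 0.243/0.736 = 0.33, giving 2 × 0.67 = 1.34. Rescaling the full 12-month count to 90 days before subtracting did better in the simulation (0.88), but still less well than covariate adjustment (0.80).

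**The case against.** The strongest reply is that this is a condensed article. It lists no adjustment covariates for any treatment-effect model, not even the urn factors, and such lists usually sit in an analysis plan that is not shown. A mixed model ANOVA does not rule out a covariate or a pre-period level. This stands to the extent that a reader might infer the plan excludes prior use; the documents do not say so. What remains is that the section fixes the response and its windows as post-discharge, and names a baseline for the drinking and PEth outcomes but not for this one.

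Second, a reader might infer that the prior-year data go unused. They do not: change in use and cost, and net benefit, both draw on them. These are separate analyses, and step 4 shows that differencing does not replace adjustment.

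Third, the size is assumed. The outcomes combine self-report with the medical record, whereas the prior year comes from the record alone. Different capture before and after would lower r. This stands, and is why the gain can only be given as a range.

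Fourth, a reader might infer that the unadjusted contrast is biased, or that a chance excess of frequent users in one arm inflates the false-positive rate. Neither follows: randomization makes the contrast valid, and its interval already allows for such imbalance.

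**Conclusion.** The point holds as an inexpensive improvement to an exploratory analysis, not as an error that threatens any conclusion. As described, the utilization models use post-discharge values with no baseline term, although a suitable pre-randomization baseline is already being extracted. The loss is precision only, and it does not touch the primary outcome.

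Its size depends wholly on the unstated r: a variance reduction of about 4% at 0.2, 9% at 0.3, 25% at 0.5 and 36% at 0.6. Under the assumed visit rates and dispersion, the gain is likely small at 34 days, possibly only 1.5%, and larger at 90 days. No claim of a large gain can be drawn from the documents.

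**What to change.** In the ED-visit and readmission models, state that the participant's value of the same measure over the 12 months before the index admission enters as a covariate: prior ED visits for ED visits, prior admissions for readmissions, prior cost for cost. Exclude the index stay from the prior window, since every participant has one. If a log-link model is adopted, log(1 + prior value) is a suitable form. Leave the change and net-benefit analyses as they are.

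The cost is one line of wording and one degree of freedom per model, with no new data. Prior use outside the hospital's record system will be missed. That reduces the gain but does not bias the contrast, because the covariate precedes randomization.
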